### Between groups comparisons

Stata version 17 will be employed for data analysis. In a comparison of demographic (sex, gender), socioeconomic (family income, parental education), behavioral characteristics (tooth brushing frequency, usage of fluoride toothpaste, dental attendance pattern, impact of oral health on daily living, sugar intake), and caries, plaque and gingival level in both primary and permanent teeth, the difference between both intervention groups will be carried out using chi-square test for categorical variables and a *t*-test for continuous variables.

We will be reporting absolute and relative measure effect, that is, absolute and relative difference in mean for continuous outcomes (changes in the number of untreated caries) and risk difference and relative risk for categorical outcomes (changes in brushing frequency, changes in plaque and gingival conditions, changes in impact of oral health on daily living). For the primary outcome (changes in the number of untreated dental caries), negative binomial regression will be used to estimate relative difference (incidence rate ratio) and predictive margin to estimate absolute difference between intervention groups. The applied analytical technique will allow accounting for stratification of the sample and clustering of children within schools and any baseline socioeconomic difference between intervention groups. For the secondary outcome, multinomial regression will be used to estimate relative risk for the changes in frequency of daily tooth brushing and changes in the perceived oral health on child’s daily life. Predictive margins will also be used to estimate absolute difference in each secondary outcome. Intention-to-treat analysis will be used to handle missing values in all outcomes.

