### Data analysis justification of sample size

Sample size was calculated based on the prevalence of untreated dental caries (84%) reported in a previous study by Adam and his colleagues (2022) among Riyadh children [31]. Considering a 95% confidence interval and 80% power, 690 children (354 individuals per arm) were sufficient to detect a clinically significant difference of 10% with design effect of two arms over a period of 36 months. The design effect was calculated as 1.44, based on an intra-class correlation coefficient of 0.02 derived from a previous study [32]. After accounting for clustering, the required number of clusters would be 20 schools and an average cluster size of 50 participants. Allowing for up to 20% dropout rate upon follow-up time, 1192 participants are required (596 per arm) [33].

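### Chi-square and t-tests that ignore school are the only tests named for plaque and gingival scores, and multinomial coefficients are presented as relative risks

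*Protocol article*

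**What the plan says.** All of the analysis text is in the protocol article under Between groups comparisons.

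- Its first paragraph lists demographic, socioeconomic and behavioural variables together with "caries, plaque and gingival level in both primary and permanent teeth". It then states that "the difference between both intervention groups will be carried out using chi-square test for categorical variables", with a t-test for continuous variables. It gives no time point and does not mention school.
- Its second paragraph promises a risk difference and a relative risk for categorical changes, among them changes in plaque and gingival condition. Caries, the primary outcome, is to be analysed by negative binomial regression. The next sentence says that the technique applied can allow for the strata, for the grouping of children in schools and for baseline socioeconomic differences.
- Only after that sentence does the text turn to secondary outcomes: "multinomial regression will be used to estimate relative risk for the changes in frequency of daily tooth brushing" and for perceived oral health in daily life. Predictive margins are then assigned to absolute differences for each secondary outcome. No model is named for plaque or gingival scores.

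Under Study design and setting and under Randomization, the school is the unit allocated. Under Secondary outcomes, changes in plaque and gingival score are listed. Under Data analysis justification of sample size, the design effect is "based on an intra-class correlation coefficient of 0.02 derived from a previous study".

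**The concern.** A chi-square test or t-test, as named, counts every child as an independent observation. Children in one school share an allocation and resemble one another, and the protocol accepts this when it sizes the trial. To allow for clustering in the sample size and then compare arms without it is inconsistent. The effect is p-values that are too small and intervals that are too narrow.

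The exposure is greatest for plaque and gingival scores, because no other analysis is named for them. Brushing frequency and quality of life do have a model, but the clustering sentence comes before that model and is not repeated for it.

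The second issue is the effect measure. An exponentiated multinomial coefficient compares the odds of one category against a base category. Reporting it as a relative risk gives readers a number that can be well away from the true ratio of proportions.

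**Working it through.** **Inputs.** From the sample size section: intra-class correlation (ICC) 0.02, stated design effect 1.44, 20 schools averaging 50 children, 1192 children in total, 20% dropout, and a 95% confidence level, taken as two-sided 5%. Allocation is 1:1 by school, so 10 schools per arm. No ICC is given for plaque, gingival or questionnaire outcomes.

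**The plan's own figure.** 690 × 1.44 × 1.2 = 1192.3, which reproduces 1192. Clustering therefore did enter the sizing, through the factor 1.44.

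**Design effect.** DE = 1 + (m − 1) × ICC, where m is children per school.
- m = 50: 1 + 49 × 0.02 = 1.98.
- m after 20% loss: 1192 × 0.8 / 20 = 47.7, so DE = 1 + 46.7 × 0.02 = 1.93.
- m with no loss: 1192 / 20 = 59.6, so DE = 1 + 58.6 × 0.02 = 2.17.
- The stated 1.44 corresponds to m = 23 at ICC 0.02, or to ICC 0.009 at m = 50. It does not match the stated ICC and cluster size taken together, so both values are carried forward.

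**True error of a nominal 5% test that ignores school.** Error = 2 × [1 − Φ(1.96 / √DE)].

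| Setting | DE | True error |
|---|---|---|
| Stated design effect | 1.44 | 10.2% |
| ICC 0.02, m = 47.7 | 1.93 | 15.9% |
| ICC 0.02, m = 50 | 1.98 | 16.4% |
| ICC 0.02, m = 59.6 | 2.17 | 18.4% |
| ICC 0.01 (assumed), m = 50 | 1.49 | 10.8% |
| ICC 0.05 (assumed), m = 50 | 3.45 | 29.1% |

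Simulation with 10 schools per arm, 50 children each and ICC 0.02 gave 16.5% for the t-test and 16.4% for the chi-square test (binary outcome, prevalence 84%). A t-test on the school means gave 4.8%.

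**Relative risk against relative-risk ratio.** The proportions below are assumed, for intervention versus control, with unchanged as the base category.
- Improved 50% v 35%, unchanged 40% v 50%. Relative risk of improvement: 0.50 / 0.35 = 1.43. Relative-risk ratio: (0.50 / 0.40) / (0.35 / 0.50) = 1.79.
- Improved 45% v 35%, unchanged 45% v 40%. Relative risk: 0.45 / 0.35 = 1.29. Relative-risk ratio: (0.45 / 0.45) / (0.35 / 0.40) = 1.14.

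The ratio equals the relative risk of the category divided by the relative risk of the base category. It is larger or smaller than the relative risk according to which way the base category moves.

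**The case against.** The strongest reply is that the first sentence describes a baseline table. It gives no time point, and it includes sex, income, parental education and sugar intake. Effect estimation starts only in the next paragraph. On that reading the tests are poor practice but inflate no treatment-effect error. This may well be the intention. The text does not say so, however, and plaque and gingival scores would then have no named analysis at all.

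A second reply is that predictive margins are promised for every secondary outcome. Margins require a fitted model, so some model for plaque and gingival scores must be intended, and a fuller document may name it. That is fair, but the article does name tests for these variables, and those tests ignore school.

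Four stronger readings are tempting, and the document does not support them:
- *The primary caries result carries the inflated error.* Caries is in the tested list, but its primary analysis is the negative binomial model, which is stated to handle clustering and strata.
- *That model uses a robust variance with a normal reference and is itself too liberal.* Neither is mentioned, and a school random effect would fit the wording equally well.
- *Covariates will be chosen by the baseline tests.* The section plans adjustment for baseline socioeconomic differences but does not say how the variables are selected.
- *The multinomial ratio always exaggerates the effect.* The second example shows the reverse.

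It is also fair to say that predicted probabilities could supply true relative risks. The text assigns margins only to absolute differences and relative risk to the regression. That brushing frequency is ordered is no error either, since a multinomial model is valid for ordered categories.

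**Conclusion.** The point holds for secondary outcomes. Followed as written, the named tests for plaque and gingival level ignore the randomised unit, and nothing extends the clustering statement to the multinomial models. If the tests are used for outcomes, the true error of a 5% test is about 16% at ICC 0.02 with 48 to 50 children per school, roughly three times nominal, and about 10%, twice nominal, at the stated design effect. A flat claim of a tripled error rate would go too far: the figure depends on which of the protocol's own values is used, and the secondary outcomes have no stated ICC (about 11% to 29% for an assumed 0.01 to 0.05 at 50 per school). These figures assume equal school sizes and treat the ICC as the correlation left within strata.

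The description of multinomial coefficients as relative risks is wrong as stated. The size and direction of the discrepancy depend on the category proportions, so the two examples are illustrations, not predictions.

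**What to change.** 1. Limit the chi-square and t-test sentence to baseline characteristics, presented descriptively by arm without significance tests.
2. State that changes in plaque, gingival condition, brushing frequency and quality of life are analysed with models that account for school and stratum and adjust for the baseline value. Keep the promised risk difference and relative risk for the categorical changes.
3. Take both relative risks and risk differences from predictive margins with school-clustered standard errors. If multinomial coefficients are shown, label them relative-risk ratios and name the base category.
4. Use a reference distribution suited to 20 schools, for example t with 17 to 18 degrees of freedom (20 schools less two arms, less one more for stratum), or give a school-level analysis as a check.

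The cost is revised wording and a little programming, with no change to trial conduct. Intervals for secondary outcomes become wider than those from tests that ignore school: by a factor of about √1.98 = 1.41 at ICC 0.02 and 50 per school, or √1.44 = 1.20 at the stated design effect, before any small-sample correction.

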### Outcomes

The combination of self-reported and clinical outcomes robust the findings on the effectiveness of virtual supervised tooth brushing. The clinical measure will be a blinded outcome measures (caries experience), plaque, and gingival scores as the examiners are blinded to the groups the children are assigned to. Unlike the clinical outcome, the self-reported frequency of tooth brushing per day and the impact of oral health on the child’s daily life (QoL) are considered a subjective measure.

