#### Secondary outcomes

Two secondary outcomes for this trial include the following: the changes in plaque and gingival score based on Leo and silence plaque and gingival index [30] and the change in the frequency of tooth brushing per day and the perceived oral health on child’s daily life (as reported by the parents).

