## Discussion

Despite the availability of free dental services in Saudi Arabia, dental caries is still a common disease among children. Many studies have focused on the implementation of school-based programs to promote and tackle the burden of untreated dental caries [34]. This study will take a step further and explore the effectiveness of virtual supervised tooth brushing on untreated dental caries especially since Saudi Arabia has proven to have an effective IT infrastructure for virtual schooling.

Three different outcome measures are used to evaluate the effectiveness of virtual supervised tooth brushing on caries experience. The study’s primary outcome is the change in caries experience—the number of decay (untreated dental caries) missing and filled teeth—in both primary and permanent teeth over 36 months (baseline, + 3 months,+ 6 months + 12 months,+ 24 months, + 36 months from baseline) using the WHO criteria [29]. The secondary outcome will be obtained through both clinical outcomes (plaque and gingival scores) and the self-reported questionnaire to assess the change in the frequency of brushing per day and the impact of oral health on the child’s daily life (QoL) [29]. The selected study design will collect data on participants’ socioeconomic and behavioral factors which will help accounting for baseline differences between the two trial groups.

The findings of this study will provide important information on the impact of virtual supervision on dental caries. A positive impact will be an opportunity for targeting a large portion of the population with a high level of disease as a quarter of the Saudi population is younger than 15 years [1]. A positive finding will also support the continuation of virtual supervised tooth brushing in many schools in other parts of the country. Finally, future research should also investigate the factors that could affect the effectiveness of programs. A national study could provide more details about the effectiveness of the program in many different parts of the country.

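### Plaque and gingival outcomes are defined as index scores, but the analysis section treats them as categorical changes with no category defined, which loses information in the only examiner-blinded secondary outcomes

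*Protocol article*

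**What the plan says.** The Secondary outcomes section defines the outcome as "the changes in plaque and gingival score based on Leo and silence plaque and gingival index". Table 1, the Data collection section and the Discussion also speak of scores. The Outcomes section groups them with the blinded clinical measures: "The clinical measure will be a blinded outcome measures (caries experience), plaque, and gingival scores as the examiners are blinded to the groups". It calls the other two secondary outcomes, brushing frequency and quality of life, subjective.

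The section Between groups comparisons assigns effect measures by type of outcome. Mean differences go to "absolute and relative difference in mean for continuous outcomes (changes in the number of untreated caries"; the caries count is the only outcome named there. Risk measures, a difference and a ratio, go to "categorical outcomes (changes in brushing frequency, changes in plaque and gingival conditions, changes in impact of oral health on daily living". Plaque and gingiva are therefore assigned to the categorical side.

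Two other sentences in that section bear on the point. One compares the groups on a list of variables that includes plaque and gingival level, using a "chi-square test for categorical variables and a *t*-test for continuous variables", without saying which test applies to which variable. The other states that "multinomial regression will be used to estimate relative risk for the changes in frequency of daily tooth brushing and changes in the perceived oral health"; it does not mention plaque or gingiva.

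**The concern.** A risk difference or relative risk needs an event or a category. To follow the analysis section, each child's numeric score has to be turned into categories of change, and the article does not say what they are. Two things follow. A child whose score falls a little and a child whose score falls a lot can count the same. The estimate also depends on where the line is drawn, and nothing in the article fixes that line before the data are seen.

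The choice falls on outcomes that matter. The hypothesis under Primary outcome rests partly on better plaque removal through correct technique, and under Data collection teeth are left uncleaned before examination because plaque is an outcome. Families know their allocation (Blinding), so the parent-reported outcomes are open to reporting bias. The plaque and gingival scores are the trial's blinded check on whether brushing improved.

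**Working it through.** **The text.** Five places treat the outcome as a score (Outcomes, Secondary outcomes, Table 1, Data collection, Discussion). One place, the effect-measure sentence in Between groups comparisons, treats it as categorical. The multinomial sentence leaves plaque and gingiva out, and the chi-square/t-test sentence does not say which applies. The only explicit statement on scale is therefore categorical.

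**No figure to reproduce.** The sample-size section (354 per arm before clustering, 596 per arm in total) concerns untreated caries. It contains no power, SD or effect for plaque or gingiva.

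**Inputs for the size of the loss**
- From the article: 20 schools, 10 per arm; 1192 / 20 = 59.6 children per school; 59.6 × 0.8 = 47.7, taken as 48 completers; ICC 0.02.
- Assumed: normal child-level scores with SD 1; ICC up to 0.05; baseline-to-follow-up correlation r of 0.3 to 0.7, the same at school and child level; two-sided 5% t-test on school means (18 df); half of control children improve.

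**Step 1, baseline-adjusted score.** The variance of the arm difference is V = (2/10)[ICC + (1 − ICC)/48](1 − r²). With 18 df, 80% power needs a noncentrality of 2.963. At ICC 0.02 and r = 0.3, V = 0.2 × 0.0404 × 0.91 = 0.00736, so the effect is 2.963 × 0.0858 = 0.254 SD.

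**Step 2, unadjusted change score.** Here 2(1 − r) replaces (1 − r²), so the noncentrality is multiplied by √[(1 + r)/2]. It becomes 2.39, 2.57 and 2.73 at r = 0.3, 0.5 and 0.7.

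**Step 3, improved yes/no.** The difference in proportions is Φ(effect/√[2(1 − r)]) − 0.5. The ICC of the binary variable is (2/π)·arcsin(ICC), which is 0.0127 for 0.02 and 0.0318 for 0.05. At ICC 0.02 and r = 0.3 the difference is Φ(0.254/1.183) − 0.5 = 0.085. Its variance is 0.2 × 0.25 × [0.0127 + 0.9873/48] = 0.00167, so the noncentrality is 0.085/0.0408 = 2.08.

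| ICC | r | adjusted score | change score | improved yes/no | cost of categorising |
|---|---|---|---|---|---|
| 0.02 | 0.3 | 80% | 62% | 51% | 11 |
| 0.02 | 0.5 | 80% | 68% | 56% | 12 |
| 0.02 | 0.7 | 80% | 73% | 61% | 12 |
| 0.05 | 0.3 | 80% | 62% | 54% | 8 |
| 0.05 | 0.5 | 80% | 68% | 60% | 8 |
| 0.05 | 0.7 | 80% | 73% | 65% | 8 |

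Simulation under the same assumptions gives 60 to 74% for the change score and 50 to 66% for improved yes/no, a gap of about 6 to 12 points.

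**Step 4, number of categories and effect size.** This is a simpler normal calculation that gives the category the same design effect as the score: 1 + 46.7 × 0.02 = 1.93, so effective n is 477/1.93 = 247 per arm. It is harsher on the category, because the binary ICC is in fact lower.
- A binary split keeps 64% of the information when even and 34% at 10/90. Three categories keep 62 to 81%.
- Where the score has 80% power, an even binary split has 60%. Three ordered categories have 59 to 71% with a trend test. An unordered two-degree-of-freedom test has 49 to 61%, so the gain depends on using the order.
- At 0.4 SD and ICC 0.02, power falls from 99% to 91 to 94% for splits from 20/80 to even. At ICC 0.05 (effective n 143) it falls from 92% to 70 to 76%, so the loss is small only at the lower ICC.

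**The case against.** The strongest reply is that this is a matter of labels in a condensed article, about outcomes the trial was not sized on, and that the power loss is the reviewer's construction. Much of this is fair.

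- The article states no cut-off, number of categories, SD or effect. Any power figure is conditional.
- A reader might infer that the plan throws away most of the power of these outcomes. The documents do not support that. Of the fall from 80% to about 51% in the worst row of the table, 18 points come from comparing an adjusted with an unadjusted analysis and only 11 from categorising.
- A reader might also infer that the plan leaves the baseline score out of the model. The article names no model or covariates for plaque and gingiva. That is silence, which a fuller plan may fill, and it is not a fault.
- The t-test sentence leaves room for a comparison of means.
- If the index is recorded as one grade per child, a categorical analysis is legitimate. The article does not say how sites are combined.

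What does not stand is the claim that nothing was fixed. The effect-measure sentence names the plaque and gingival changes as categorical and assigns them risk measures. That is a stated rule, it conflicts with the outcome definition, and no other sentence replaces it.

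**Conclusion.** The point holds as a conflict between the definition of the outcome and its stated analysis, with a moderate and conditional cost. Plaque and gingival outcomes are defined as scores and then assigned to categorical reporting without a category. This discards information and leaves the result dependent on an unstated cut-off. Under the assumptions listed, categorising alone costs about 6 to 12 power points where a baseline-adjusted score analysis would have 80%. In the table that corresponds to effects of about 0.19 to 0.33 SD. The cost is lower with three ordered categories and small for effects of 0.4 SD or more at ICC 0.02. More extreme cut-offs cost more. Normality of the child-level score is assumed. The primary outcome and the sample size are not affected, but the scale should be settled because these are the only examiner-blinded secondary outcomes.

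**What to change.** In Between groups comparisons, move the plaque and gingival scores from the categorical to the continuous outcomes. Report the mean difference between arms with a 95% CI from a model with arm, the child's baseline score, affluence stratum and school clustering. Keep any improved/not improved table as description only. If the index yields only a single grade per child, use an ordinal model with the same terms.

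The cost is a change of analysis wording. No new data, visits or participants are needed, and readers who want a risk-type figure still have the descriptive table.

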**Methods:**

This is a cluster randomized controlled trial comparing a virtual supervised tooth brushing program against no intervention applied. A total of 1192 (596 in each group) 8–9-year-old children in Riyadh primary schools, Saudi Arabia, will be recruited for the trial. Schools (cluster) will be randomly selected and allocated to either group. Clinical assessment for caries experience will be conducted in six points (baseline, + 3 months, + 6 months, + 12 months, + 24 months, + 36 months) by dental hygienists using the World Health Organization criteria. Data on sociodemographic behavioral factors and children’s quality of life will be collected with every clinical assessment through a structured questionnaire. The primary outcome is the change in caries experience (the number of teeth with untreated dental caries, filled and missing teeth) in both primary and permanent teeth over 36 months.

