### Trial interventions

Oral epidemiological assessment will be conducted in-person in the preventive dentistry clinics to all children within both groups (intervention and control group). The difference between the two groups lies in that the intervention group will receive virtual supervision on tooth brushing once a week by the dental hygienist through “Mawid” a Ministry of Health (MOH) Central Appointment System and for 4 days during the week they are provided with different videos of the correct tooth brushing method. The video will be sent via “SMS” to the parents of students on a daily basis; thus, a reminder was not considered. This continues for three consecutive months.

Appointments will be booked via “Mawid” with is a (MOH) Central Appointment System and mobile application for managing appointments in primary healthcare centers and hospitals nationwide [25], while the virtual appointments will be conducted using “Sehhaty,” a public mobile application integrated with “Mawid” used for various health services such as sick leave, e-prescription, and managing in-person and virtual appointments nationwide [26]. All virtual appointments during the study will be booked accordingly and subjects will receive an SMS with the date and time of his/her appointment and a link on how to use the service [27]. The virtual appointments will be conducted using the collaboration of two national platforms. “Sehhaty” is to be used by the subjects. And “ANAT” is to be used by the physicians, whereas “ANAT” is an MOH-approved platform used for virtual consultations booked in both “Mawid” and “Sehhaty” [28].

A comparison against a control with no intervention was not considered due to ethical concerns (children would be examined but not informed about their oral findings). Thus, children in both groups will be informed about their oral findings and will be educated about how to make an appointment through “Sehhaty” application; all treatment will be provided free of charge. It is worth noting that both groups will receive fluoride toothpaste (1450 ppm) along with the examination received. In this trial, we will consider those with untreated dental caries as screened positive children, whereas all others will be considered as a screened negative children, based on the World Health Organization (WHO) criteria [29]. At the time of examination, parents or caregivers will be provided an electronic WHO questionnaire to filled out [29].

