#### Primary outcome

The study’s primary outcome is the change in caries experience—the number of decayed (untreated dental caries) missing and filled teeth—in both primary and permanent teeth over 36 months. The underlining assumption of the selected primary outcome is that children in the intervention group will be exposed to more fluoride (toothpaste daily exposure) in addition to mechanical tooth cleaning (correct dental plaque debridement through correct brushing technique) during the trial period leading to a fewer incidence of dental caries than those in the control group.

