**Assessment (both intervention arms)**								
Parental Questionnaire: Sociodemographic data	**X**		**X**	**X**	**X**	**X**	**X**	**X**
Parental Questionnaire: Behavioural data	**X**		**X**	**X**	**X**	**X**	**X**	**X**
Primary outcome: clinical examination (untreated dental caries)			**X**	**X**	**X**	**X**	**X**	**X**
Secondary outcome: clinical examination (gingival and plaque score)			**X**	**X**	**X**	**X**	**X**	**X**
Secondary outcome: frequency of daily toothbrushing	**X**		**X**	**X**	**X**	**X**	**X**	**X**
Secondary outcome: impact on quality of life (parental repots)	**X**		**X**	**X**	**X**			**X**

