A total number of 40 dental hygienists will be included in this trial under the supervision of the principal investigator. Twenty dental hygienists performing the clinical examination in the Ministry of Health Primary Health Care Centres will be trained and calibrated before the beginning of the trial. The other 20 dental hygienists will be responsible for virtual supervised tooth brushing where two dental hygienists be assigned to each school (2:1 ratio).

Clinical examination for caries experience will be performed according to the WHO criteria that define dental caries at caries into dentine threshold [29]. No radiographs will be taken. Examination will be conducted similarly at baseline and all following follow-ups (+ 3 months, + 6 months, + 12 months + 24 months, + 36 months from baseline). Examination will be performed in a dental clinic on dental chair using an examination kit that includes a plane mouth mirror and a periodontal probe. Teeth will not be brushed or cleaned prior to the examination as plaque score is an outcome of interest. During the examination, air will be applied to better assess the plaque; this will be followed by removal of debris using gauze and cotton roll to facilitate visual inspection and assess gingival score and dental caries. Standard infection control will be in place.

After each clinical examination phase (baseline, (+ 3 months, + 6 months, + 12 months, + 24 months, + 36 months), 10% of children will be re-examined to assess inter-examiner reliability. Children with identified positive caries will be informed, and parents will be instructed to book an online appointment through Mawid. Given the training in oral health condition assessment, the probability of false positive caries cases is minimal. Yet, upon the booked appointment by the parents, a standard dental check-up is always conducted as part of the treatment plan where any false-positive cases will be identified. If that is the case, the dentist will inform the parents that no further treatment is required.

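### The primary outcome is defined as decayed, missing and filled teeth, but the primary model and Table 1 use untreated caries alone, a count that also moves with dental treatment

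*Protocol article*

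**What the plan says.** The document gives the primary outcome in three forms.

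- **Three-component count.** The Primary outcome section takes change over 36 months, in primary and permanent teeth, in "the number of decayed (untreated dental caries) missing and filled teeth". The Abstract (Methods) has "the number of teeth with untreated dental caries, filled and missing teeth", and the Discussion has "the number of decay (untreated dental caries) missing and filled teeth". The Blinding section also says that caries experience was chosen as primary.
- **Untreated caries only, as a count.** Between groups comparisons specifies the negative binomial model, incidence rate ratio and predictive margins with the words "For the primary outcome (changes in the number of untreated dental caries". Just before that, it gives the number of untreated caries as its example of a continuous outcome. The Table 1 row reads "Primary outcome: clinical examination (untreated dental caries".
- **Untreated caries only, as a proportion.** The sample size section starts from an 84% prevalence of untreated caries.

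The same document describes a route to treatment for both arms. Data collection says: "Children with identified positive caries will be informed, and parents will be instructed to book an online appointment through Mawid". Trial interventions says that "all treatment will be provided free of charge". The note under Table 1 has both groups advised to book according to need.

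**The concern.** The two counts are different variables, and in this trial they can move apart. Filling or extracting a decayed tooth removes it from the untreated count and moves it to the filled or missing component, so the three-component total does not change. The Primary outcome section states the hypothesis as fewer new caries, through fluoride exposure and plaque removal. A model of untreated teeth does not test that hypothesis cleanly, because its result also depends on how many decayed teeth have been treated by the time of the examination.

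The choice of primary variable is also left open. A later plan could adopt either variable and claim to follow this document. The Discussion would use a positive result to support continuing the programme in other schools, so it matters which quantity was tested.

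**Working it through.** **1. Is it shorthand?** The Primary outcome section uses the term untreated dental caries to explain the decayed component, then lists missing and filled separately. By the document's own vocabulary, the analysis section and Table 1 name one component of three. No model is given for the three-component count.

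**2. What the sample size is built on.** Inputs from the sample size section: 690 children before clustering, design effect 1.44, dropout 20%.

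690 × 1.44 = 993.6; 993.6 × 1.2 = 1192.3, against the stated 1192.

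This last step reproduces. The 690 does not reproduce exactly from two proportions at 80% power and a two-sided 5% level (sidedness assumed):
- 84% against 74% needs 260 per arm, 520 in total.
- 84% against 75.6% (10% relative) needs 358 per arm, 716 in total.

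Either way, the basis is a binary outcome. The document gives no mean or dispersion for any tooth count, so power for a count outcome cannot be computed from it.

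**3. How treatment enters the untreated count.** Let B be decayed teeth at baseline, I new decayed teeth by 36 months, and u the share of decayed teeth treated by then. The same u is applied to old and new lesions, and shedding is ignored.

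- Untreated count at 36 months = (B + I)(1 − u)
- Rise in decayed + missing + filled = I, whatever u is

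*Equal uptake in both arms.* The absolute difference in untreated teeth is (I_ctrl − I_int)(1 − u). With u = 20% to 40%, 80% to 60% of the true absolute difference remains. The ratio of the two counts does not change, and no false effect arises.

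*Unequal uptake, no preventive effect.* With the same B and I in both arms, the ratio of untreated counts is (1 − u_int)/(1 − u_ctrl), whatever the caries level.

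The document gives neither mean counts nor uptake, so every input below is an assumption: B = 4, I = 2, and uptake as shown.

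| u control | u intervention | Untreated, control | Untreated, intervention | Ratio | Rise in caries experience, both arms |
|---|---|---|---|---|---|
| 20% | 20% | 4.8 | 4.8 | 1.000 | 2 |
| 20% | 30% | 4.8 | 4.2 | 0.875 | 2 |
| 20% | 40% | 4.8 | 3.6 | 0.750 | 2 |
| 30% | 40% | 4.2 | 3.6 | 0.857 | 2 |
| 30% | 50% | 4.2 | 3.0 | 0.714 | 2 |
| 40% | 50% | 3.6 | 3.0 | 0.833 | 2 |
| 40% | 60% | 3.6 | 2.4 | 0.667 | 2 |

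**4. Sign of a change score.** At 40% uptake the change in untreated teeth is 3.6 − 4 = −0.4. A negative binomial model cannot take negative values. The three-component count can fall too: children enter at 8 to 9 years, primary teeth are included, and follow-up is 36 months. A decayed or filled primary tooth that is shed leaves the count unless it is scored as missing.

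**The case against.** The strongest defence is that untreated caries is a loose label for caries experience, since Data collection describes the examination as one for caries experience. That reading is weak. The model sentence and the Table 1 row both use the narrower term, and the outcome section reserves that term for one component. An analysis plan that is not shown may settle the matter, but it would not remove two conflicting statements from this document.

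A reader might infer that treatment uptake will be higher in the intervention arm, because those children meet a hygienist weekly through the booking system also used for treatment, and that the trial is therefore headed for a false positive. The document does not support this:
- Mawid is used to book every child's examination and to book treatment in both arms.
- The virtual sessions run on Sehhaty and ANAT.
- Both arms receive the same findings, booking instructions and free treatment.
- Supervision concerns brushing and lasts three months of a 36-month follow-up. Nothing says that the sessions promote treatment.

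Families are unblinded, so unequal uptake cannot be excluded, but it remains a possibility only.

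It is also tempting to compare an assumed gap in untreated teeth with the 2.92 versus 2.60 reported for the London supervised-brushing trial in the Background. That figure is a caries increment under daily in-person supervision, not a standing count of untreated teeth, so it is no yardstick here.

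Nor must the untreated count fall when children are treated, since new lesions can offset treatment. Referral after the 36-month examination cannot affect the 36-month outcome.

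**Conclusion.** The contradiction stands in the current text and needs correcting: the specified primary model does not analyse the stated primary outcome. It rests on the wording alone and needs no assumption.

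That the untreated count mixes treatment with prevention follows from its definition together with the treatment route open to both arms. The size of the effect is illustrative. Under the simple model above, equal uptake of 20–40% leaves 80–60% of a true absolute difference. An assumed excess of 10–20 points in the intervention arm gives ratios of 0.875 to 0.667 with no prevention. The direction and existence of any difference in uptake between arms are unknown, so dilution is the firmer consequence and a false difference the conditional one.

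**What to change.** 1. In Between groups comparisons and in the Table 1 row, make the primary variable the 36-month caries-experience outcome of the Primary outcome section (decayed, missing and filled teeth). Correct the earlier mention in the analysis section that gives untreated caries as the continuous outcome.
2. Report untreated caries as a secondary outcome, labelled as also reflecting treatment received.
3. Give the negative binomial model a non-negative response: either the count of teeth newly affected since baseline, or the 36-month count adjusted for the baseline count. A raw change score is unsuitable. State how shed primary teeth are counted.
4. State in the sample size section that the figure was derived for the prevalence of untreated caries and not for this count.

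The cost is small. The components come from the same examination, so no new data are needed and the arrangements for informing and referring children are unaffected. It is slightly more than a wording change, because the response variable of the model must be restated and the sample-size basis becomes less direct for the chosen outcome.
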